#### Effectiveness of the PCMed Service (secondary aims)

Secondary outcomes include the self-reported use of RRMeds by clients and the reason for not using RRMeds at 6 months after the PCMed Service consultation, where a decision was made regarding whether or not to take RRMeds. These data are obtained through a follow-up telephone call and include (where relevant) whether RRMeds were commenced, the medication commenced, the date of commencement, whether RRMeds were ceased and the reason for ceasing. For women who did not commence RRMeds, data are collected on the reason(s) for not using RRMeds, their intent to use RRMeds in the future, the reason for not intending to use RRMeds (if relevant) and factors that would facilitate use of RRMeds.

#### Adoption of the PCMed Service

To what extent the PCMed Service intervention is adopted will be measured by the attendance of clients at the Service within 6 months following a documented discussion about the Service at the relevant catchment clinic.

#### Acceptability of the Service

Quantitative and qualitative data are collected to explore acceptability for both clients and clinicians. Acceptability of the Service to clients is measured using a brief survey based on the theoretical framework of acceptability (TFA).^39^ This comprises seven constructs (affective attitude, self-efficacy, burden, intervention coherence, perceived effectiveness, ethicality and opportunity cost) that guide the assessment of a client’s perception of acceptability.^39^ The survey is sent to clients 2–3 weeks after the PCMed Service consultation where a decision was made on whether to take RRMeds or not. If no response is received, two reminders are sent out at 1–2 weeks, and then 3–4 weeks after the initial invitation was sent.

A subset of clients are invited to participate in semistructured phone interviews after their last consultation in the PCMed Service. The purpose is to interrogate the acceptability survey findings of the PCMed Service for the study sample. An interview guide was developed based on the constructs of the TFA^39^ thought to be most relevant to the PCMed Service intervention (ie, affective attitude, self-efficacy, burden, intervention coherence and perceived effectiveness). The interview guide was pilot tested on the first two clients, with questions subsequently refined.

A purposive sampling framework, using quota sampling,^40^ will be used to ensure a representative cross-section of the sample population based on age (20–39 years, 40–55 years and >55 years), residence (defined using the Accessibility/Remoteness Index of Australia^41^) and referring clinic. To achieve ‘theoretical saturation’, it is estimated that a sample size of 15–20 clients is needed. However, saturation will be assessed through preliminary analysis, and data collection will continue until saturation is reached.^42 43^

Acceptability of the Service to clinicians will also be measured using a brief survey based on the TFA.^39^ A subset of clinicians will be invited to participate in a semistructured telephone interview. A separate interview guide for clinicians, based on the constructs of the TFA,^39^ has been developed which will further explore clinicians’ experiences and the acceptability of the PCMed Service, including the referral process and any interactions with the Service. The interview guide will be piloted with the first clinician and refined as required. A purposive sampling framework has been devised, using quota sampling^40^ to ensure a representative cross-section of clinicians based on clinic type, specialty and sex (male/female). Clinicians will be recruited until saturation of themes is reached, and it is estimated that a sample size of 15–20 clinicians is needed.^42 43^

#### Feasibility and fidelity of the PCMed Service

Data are being collected on the number of consultations delivered by telehealth versus face-to-face versus telephone; the type of clinician leading the consultation (nurse practitioner versus medical oncologist); the duration of each consultation; how many consultations were required before a prescription was written for RRMeds or the client was discharged from the Service; the number of clients who failed to attend the planned postprescription consultation and the self-reported reason; the number of additional postprescription reviews required. Utilisation of the telephone hotline service is also being recorded, including the number of calls received, the duration of each phone call, the caller type (eg, client, referring clinician and PCP) and the self-reported reason for the call. Any unintended consequences or deviations from the planned processes in the delivery of the PCMed Service are being documented by the nurse practitioner in a research journal as the events occur.

#### Cost of the PCMed Service

The cost to deliver the PCMed Service will be evaluated by comparing the average funding received per client who attended the PCMed Service with the average cost per client of providing the Service.

Services provided in Australian public hospitals, including PMCC, are funded using an activity-based funding model,^44^ with payment based on service activity (ie, the number and type of service provided).^44^ It uses national classifications for services and prices, all set in Australia by the Independent Health and Aged Care Pricing Authority.^45^ The PCMed Service activity is captured in the PMCC database management systems. The Service activity will be extracted at the end of the study period, and a monetary figure allocated to the activity so the funding received can be calculated.

Data used to calculate the cost of service delivery will include the number and duration of all consultations (including calls to the hotline telephone service) and the attending clinician (nurse practitioner or medical oncologist). Cost per client consultation is calculated by multiplying the duration of the consultation by the hourly cost of the nurse practitioner or medical oncologist, respectively. A reasonable estimate of time spent by an administration officer per client (eg, making appointments, sending notifications) will be used. If an interpreter was used, the cost of the interpreter service will be added. Consultation cost, administration officer cost and interpreter cost will be summed into a total cost per patient.

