**Figure 2 F2:**
[figure not shown]
(A) Preservice work-up: referrals are reviewed by the nurse practitioner ([name]). Women who meet preliminary eligibility criteria are sent a questionnaire (regarding demographics, social and medical history, breast cancer risk factors and willingness to consider RRMeds). Breast cancer risk is determined using validated risk prediction models/tools such as iPrevent,^32^ Tyrer Cuzick,^33 34^ or the Breast and Ovarian Analysis of Disease Incidence and Carrier Estimation Algorithm (BOADICEA)^35 36^,unless there is a history of thoracic radiotherapy, in which case risk is estimated using published data.^37^ For women referred from services external to catchment clinics, the iPrevent^32^ prediction model is applied. Eligible women are offered an appointment in the Service. (B) PCMed Service attendance: in the initial telehealth appointment, clients receive a discussion of their personalised breast cancer risk. If a client desires, their 10-year, 20-year or remaining lifetime risk is conveyed as a numerical value. The names and mechanism of action of potentially appropriate RRMeds, the absolute risk reduction that could be achieved with RRMeds, and other benefits and any potential adverse effects of RRMeds are discussed. Client understanding of the information received is assessed. A second consultation is offered for clients requiring more time to decide on whether to take RRMeds. Clients who desire RRMeds receive a prescription and are booked for review in 8–10 weeks to assess and manage any side effects. If tolerating the RRMed, care is transferred to the PCP with additional information and instructions to continue management. (C) Postservice support: a hotline telephone service is provided for clinicians and clients to address any concerns relating to side effects, and additional appointments are made if required. PCMed, Preventing Cancer with Medications; PCP, primary care physician; RRMeds, risk-reducing medications.

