### Aims

The overarching aim is to evaluate the effectiveness and process of implementing this new clinical service.

The primary aim is:

To determine whether the PCMed Service is associated with an increased use of RRMeds by women who attend catchment clinics, compared with use by similar women who attended catchment clinics before the implementation of the PCMed Service.

Secondary aims include:

To describe the adoption of the PCMed Service by women who attend catchment clinics. Specifically, the proportion of eligible women who attend the PCMed Service following a catchment clinic appointment where the PCMed Service is discussed.To determine the uptake of RRMeds for all clients who attend the PCMed Service and the associated characteristics.To explore the reasons for not taking up RRMeds and the associated characteristics.To explore the acceptability of the PCMed Service to clients.To explore the acceptability of the PCMed Service to clinicians.To determine the feasibility and fidelity of the PCMed Service intervention and any adaptations required.To evaluate the cost of delivering the PCMed Service from the perspective of the healthcare provider.

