### Recruitment to the PCMed Service and study

Prior to the commencement of the PCMed Service, clinicians working in the catchment clinics, including breast care nurses, were informed of the PCMed Service and its concurrent evaluation. Resources were developed and placed in the catchment clinics. These include a client brochure and a clinician fact sheet that describes the Service, eligibility criteria and the referral process.

Eligible women are actively recruited for the PCMed Service from catchment clinics by the nurse practitioner ([name]), who reviews the electronic medical records of women in advance of their catchment clinic appointment and identifies those who are potentially eligible for the PCMed Service. Clinicians seeing these women are reminded by [name] of the PCMed Service and asked to provide eligible women with a client brochure and to refer them to the PCMed Service if appropriate.

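### The cost sum omits clinician time for the pre-service work-up, so delivery cost is understated and the funding balance overstated by an amount the protocol does not allow us to size

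*Protocol article*

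**What the plan says.** The last secondary aim in the protocol article (Aims) is "To evaluate the cost of delivering the PCMed Service from the perspective of the healthcare provider". Under Outcome measures, Cost of the PCMed Service, average funding per attending client is compared with average cost per client. The matching section under Analysis of secondary outcomes takes the difference of the two.

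The cost side is built from three parts:

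- Clinician time: "Cost per client consultation is calculated by multiplying the duration of the consultation by the hourly cost of the nurse practitioner or medical oncologist". The consultations counted are described as "including calls to the hotline telephone service".
- Administration: "A reasonable estimate of time spent by an administration officer per client (eg, making appointments, sending notifications) will be used".
- Interpreter cost, where an interpreter was used.

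The rule then closes: "Consultation cost, administration officer cost and interpreter cost will be summed into a total cost per patient".

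Figure 2 describes the intervention in three parts: (A) pre-service work-up, (B) attendance and (C) post-service support. In part A, "referrals are reviewed by the nurse practitioner", a questionnaire is sent, and "Breast cancer risk is determined using validated risk prediction models/tools such as iPrevent" or a similar tool. The section Recruitment to the PCMed Service and study adds that the nurse practitioner "reviews the electronic medical records of women in advance of their catchment clinic appointment and identifies those who are potentially eligible", and reminds the clinicians who will see these women.

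**The concern.** Parts B and C of the intervention are costed through consultation and hotline time. Part A has no clinician line, although at least one of its tasks is assigned by name to the nurse practitioner. A provider pays for those hours whether or not the client is on the call. Leaving them out therefore moves the result in one direction only: cost looks lower and the funding balance looks better.

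The Discussion presents the cost evaluation as important for sustainability and as an input to later implementation and economic evaluation. A site that budgeted from the reported cost per client would allow too little clinician time.

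**Working it through.** The article gives no cost figure, hourly rate, consultation length or funding amount, so there is nothing to reproduce. The check compares the described activities with the stated sum.

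**1. Activities against the sum**

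| Activity | Described in | Who does it | In the sum? |
|---|---|---|---|
| Referral review | Figure 2, part A | Nurse practitioner (stated) | No |
| Questionnaire sent out | Figure 2, part A | Not stated | Possibly, as administration officer time |
| Risk-model estimation | Figure 2, part A | Not stated | No |
| Consultations and reviews | Figure 2, parts B and C | Nurse practitioner or medical oncologist | Yes |
| Hotline calls | Figure 2, part C | Clinician taking the call | Yes |
| Record screening and clinician reminders | Recruitment to the PCMed Service and study | Nurse practitioner (stated) | No |

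**2. Could data collected elsewhere fill the gap?** The section Feasibility and fidelity of the PCMed Service (Outcome measures) records the duration of consultations and of hotline calls. It lists no time for referral review or risk estimation.

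**3. Direction.** Let F be funding per attending client, C the cost under the stated sum, and P > 0 the cost of the omitted work-up time.

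- Reported balance: F − C.
- Balance with work-up included: F − (C + P).
- Difference: (F − C) − (F − C − P) = P.

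Cost is too low by P and the balance too high by the same P, whatever F and C are.

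**4. Size, on assumed minutes only.** Let p be the omitted and k the counted clinician minutes per client, at one hourly rate. The share of clinician time left out is p/(p + k).

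- p = 10, k = 120: 10/130 = 7.7%
- p = 10, k = 60: 10/70 = 14.3%
- p = 30, k = 90: 30/120 = 25.0%
- p = 60, k = 120: 60/180 = 33.3%
- p = 60, k = 60: 60/120 = 50.0%

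None of these minutes come from the documents. The shares refer to clinician time. As shares of total cost they would be smaller, because administration and interpreter cost enlarge the denominator.

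**5. Referred women who do not attend.** If a fraction a of the women worked up attend, work-up time per attending client is p/a. At an assumed a = 0.7, 10 minutes becomes 10/0.7 = 14 and 60 minutes becomes 60/0.7 = 86. Whether to count this time is a choice of costing boundary.

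**The case against.** The case against has several parts.

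- **A condensed article may leave costing detail elsewhere.** It does not say whether the hourly cost is loaded for non-contact time, or whether duration includes preparation. If either held, some of the gap would close. That is possible, but the article states neither, and it does state which components make up the total. The protocol's statement that the data will include certain items describes inputs; it does not add a component to the closed sum.
- **Not all of part A is shown to be uncosted clinician work.** A reader might infer that the whole work-up is unpaid nurse practitioner time. The text does not support that. The role is named only for referral review; sending the questionnaire could fall under the open-ended administration examples; and no one is named for risk estimation. The primary-outcome section says familial cancer clinics already apply BOADICEA routinely, so the Service's extra time for those women may be small. This objection stands and narrows the point.
- **Record screening and reminders are arguable.** The text describes recruitment for the Service, which favours counting them. They can also be read as case-finding tied to launch and evaluation. Their omission is a boundary choice, not an error.
- **The comparison itself is consistent.** A reader might infer that cost per attending client is set against all funding received. It is not: both cost sections put both sides on attending clients.
- **The stakes are moderate.** Cost is the last secondary aim, is analysed descriptively with no decision threshold, and does not touch the primary outcome.

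Referral review survives all of these. It is clinician work by the protocol's own description and has no place in the sum.

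**Conclusion.** The point holds in a limited form. As written, total cost per patient omits clinician time for pre-service work-up: at least the nurse practitioner's referral review, and any risk estimation that the Service performs itself. From the provider's perspective, delivery cost is understated and the funding balance overstated by the value of that time. The direction follows by arithmetic for any positive omitted time. It assumes that the hourly cost and the recorded durations do not already cover preparation, and the article gives no sign that they do.

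The size cannot be derived from the documents, and the illustrative shares above are not estimates. It is tempting to add that the omission could turn a deficit into an apparent surplus. The documents give no funding or cost amount, so nothing shows that the balance is close to zero, and that inference should not be drawn.

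This should be corrected before the cost analysis. It does not affect the validity of the primary comparison.

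**What to change.** Add one component to the sum in Cost of the PCMed Service (Outcome measures): clinician time for pre-service work-up, meaning referral review and any risk estimation done by the Service, multiplied by the hourly cost of the clinician who does it. A staff estimate or short time log is enough, since the plan already accepts an estimate for the administration officer. Report a low and a high value. State whether hourly cost or consultation duration already includes preparation, so that no time is counted twice.

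Show separately, as a sensitivity analysis, the work-up of referred women who do not attend, and the record screening and clinician reminders. These depend on where the costing boundary is drawn.

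If work-up time cannot be estimated, label the total as direct consultation cost (with its administration and interpreter components) and do not present the difference as the Service's full funding balance.

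The price is a small time log or estimate, one more line in the calculation, and a less favourable reported cost per client.

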### Statistical considerations and analyses

#### Sample size considerations

The prospective sample size required for the primary outcome will depend on the uptake of RRMeds in the historical cohort. We will identify 100 consecutive historical controls. Based on Australian data,^25^ we expect the uptake of RRMeds in the historical cohort to be 2%. Based on the clinical judgement of the investigators, we consider an increase from a baseline of 2%, prior to the commencement of the PCMed Service, to 20% after its implementation to be clinically significant enough to warrant implementation of this complex intervention. A prospective sample size of 57 clients who attend the PCMed Service from catchment clinics will be required to provide 80% power to detect a minimum change from 2% to 20% at a 5% significance level. To account for a possible 10% loss to follow-up, we will recruit a sample of 63 consenting clients from catchment clinics as they attend the PCMed Service. If the uptake of RRMeds (in the historical cohort) is substantially different from 2%, the prospective sample size will be adjusted.

Recruitment to the Service and the study commenced on 14 November 2023. To date, 100 women (historical controls) have been recruited to the retrospective component of the study and 278 women to the prospective component of the study. Thirty-five of the prospectively recruited women are eligible for the analysis of the primary outcome; the remainder are eligible for other outcome analyses.

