#### Inferential statistics

Comparisons of event proportions between the prospective cohort and historical controls will be conducted using a χ^2^ test, Fisher’s exact test or linear mixed modelling as appropriate. Associations between participant characteristics and study outcomes will be explored using univariable and multivariable logistic, Poisson and/or negative binomial regression and/or linear mixed modelling as indicated. Multivariable models will be assessed for collinearity and interactions between explanatory covariates. Adjustment for clinic effects will be conducted by including the clinic identifier as a random effect in the aforementioned models. The final selection of test or model type will be confirmed on initial review of the collected data, with consideration given to the number of available events for each outcome. For all analyses, p<0.05 will be considered significant. All analyses will be undertaken using R statistical computing software, V.4.4.2^46^ and/or Stata, statistical software, V.18.^47^

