#### Analysis sets

The analysis for the primary outcome will include all clients from catchment clinics who attend the PCMed Service and historical controls. A sensitivity analysis will consist of all eligible women attending catchment clinics from the commencement of the study period, regardless of whether they attended the PCMed Service, and historical controls.

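### 57 clients for 80% power is an equal-groups figure; against the 100 fixed historical controls it gives about 95–97% power, so the stated power and required size are wrong

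*Protocol article*

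**What the plan says.** All the planning figures stand in the protocol article under Sample size considerations.

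- The control group is fixed: "We will identify 100 consecutive historical controls". The same section reports that all 100 have been recruited.
- Historical uptake is expected to be 2%. An uptake of 20% is taken, on clinical judgement, as enough to justify the service.
- The prospective size follows: "A prospective sample size of 57 clients who attend the PCMed Service from catchment clinics will be required to provide 80% power". The contrast is the one just given, tested at the 5% level, and the article calls the step from 2% to 20% a minimum change. An allowance of 10% for loss to follow-up takes the 57 to 63.
- If historical uptake turns out substantially different from 2%, "the prospective sample size will be adjusted".

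Analysis sets defines the comparison: "The analysis for the primary outcome will include all clients from catchment clinics who attend the PCMed Service and historical controls". Inferential statistics names the candidate tests: "Comparisons of event proportions between the prospective cohort and historical controls will be conducted using a χ^2^ test, Fisher’s exact test or linear mixed modelling". It also sets the criterion: "For all analyses, p<0.05 will be considered significant". The article gives no sample-size formula, sidedness or allocation ratio, and nowhere mentions a 1:1 comparison or a subset of 57 controls.

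**The concern.** Power for two proportions depends on both group sizes. With 100 controls in place, the only unknown is the number of clients, and that number should be smaller than the per-group size of an equal-groups design whenever the latter is below 100. A requirement of 57 looked too large for a contrast as wide as 2% versus 20% against 100 controls.

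If 57 was calculated for equal groups, three statements about the primary outcome are wrong: the power, the number of clients required, and the description of 2% to 20% as the minimum change detected. The method matters beyond the present figure, because the section promises to revise the prospective size once historical uptake is known.

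**Working it through.** **Inputs.** p1 = 0.02, p2 = 0.20, difference 0.18, 5% significance, 80% power, 100 controls, 57 clients (all from Sample size considerations). Two-sided testing is assumed, as sidedness is not stated. The figures are for an unadjusted comparison.

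**Step 1. Reproduce 57.** For equal groups the mean proportion is 0.11, and the uncorrected size per group is

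n = [1.960·√(2 × 0.11 × 0.89) + 0.842·√(0.02 × 0.98 + 0.20 × 0.80)]² / 0.18² = (0.8673 + 0.3567)² / 0.0324 = 46.2.

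The continuity correction gives

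(n/4)·[1 + √(1 + 4/(n × 0.18))]² = 56.8, hence **57 per group**.

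The other equal-groups variants tried do not match: 47 (two-sided, uncorrected), 37 or 47 (one-sided, without and with correction), 38 (arcsine), about 52 (Fisher). With 100 controls, no variant tried gives 57.

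**Step 2. Same formula, actual allocation.** With k = 57/100 = 0.57, the correction term is a = (1 + 1/k)/0.18 = 15.30. The effective control size is (100 − a/2)²/100 = 85.3. The pooled proportion is (0.02 + 0.57 × 0.20)/1.57 = 0.0854. Then

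z = [0.18·√85.3 − 1.960·√((1 + 1/0.57) × 0.0854 × 0.9146)] / √(0.0196 + 0.16/0.57) = 1.37,

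which gives power of **91.5%**. At 57 versus 57 the same calculation returns 80.2%.

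**Step 3. The planned tests.** Power was found by enumerating every pair of outcomes from the two binomial distributions.

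| Controls v clients | Fisher | Corrected χ² | Uncorrected χ² | Corrected formula |
|---|---|---|---|---|
| 57 v 57 | 85.3% | 85.3% | 92.7% | 80.2% |
| 100 v 57 | 96.6% | 94.9% | 97.5% | 91.5% |
| 100 v 63 | 97.4% | 96.5% | 98.3% | 93.0% |
| 100 v 35 | 89.7% | 86.8% | 92.4% | 82.6% |

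**Step 4. Clients needed for 80% power against 100 controls.** The uncorrected formula gives 21, Fisher about 23–25 (exact power is not monotone in n), the corrected formula 32, and an unpooled-variance formula 41. None is near 57.

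**Step 5. Uptake detectable with 80% power at 57 v 100.** Fisher's test has 80.2% power at 14%. The corrected χ² has 79.2% at 15%. The corrected formula has 80.1% at 16%.

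**Step 6. What resizing would do.** These are corrected-formula sizes for 80% power, assuming the 20% target is kept.

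| Historical uptake | Equal-groups size | Size needed v 100 controls |
|---|---|---|
| 3% | 66 | 41 |
| 5% | 88 | 75 |
| 6% | 104 | 108 |
| 8% | 147 | 340 |

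At 8%, recruiting 147 clients against 100 controls would give about 68% power.

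**The case against.** The best defence is that the error is harmless. Under the stated assumptions the primary comparison is better powered than claimed, the controls are already collected, and neither the test nor the estimand changes. That is correct, and it limits the weight of the point.

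A second argument is that the surplus may be wanted. Inferential statistics plans a clinic random effect, and the primary analysis plans covariate adjustment; both could cost power. By the corrected formula, an assumed design effect of 1.3 lowers 57 v 100 to 82.5%, and 1.5 lowers it to 76.3%. A higher baseline also uses up the margin: at 5% historical uptake, power is 79.8% (Fisher) or 73.9% (corrected formula). So 95–97% must be labelled as unadjusted and conditional on 2%. But the section allows only for loss to follow-up. If a margin for clustering or adjustment was intended, the text does not say so; it says 80%.

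Third, part of the rise from 80% to 95–97% comes from changing method, since exact Fisher power at 57 v 57 is already 85.3%. This is fair. The like-for-like figure is 91.5%, and it leads to the same conclusion.

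Fourth, the equal-groups origin is inferred from an exact numerical match, and no resizing formula is given, so repetition of the error is a risk and not a certainty. Also, the 35 women described as eligible for the primary analysis need not have completed 12 months. After 10% loss they would number about 31–32, roughly the 80% threshold by the corrected formula. Their number should not be read as showing that recruitment could stop.

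**Conclusion.** The point holds. The article's own inputs do not give 80% power at 57 clients. They give about 95–97% with the χ² and Fisher tests it names, and 91.5% with the formula that reproduces 57. The size required for 80% is about 23–25 by Fisher's test or 32 by the corrected formula, and at most 41 by any variant tried. The uptake detectable with 80% power at 57 clients is about 14–16%, depending on method, not 20%.

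These results assume two-sided 5% testing, a true historical uptake of 2%, 57 evaluable clients and no loss of power from clinic effects or adjustment. The error is conservative at 2% and does not invalidate the primary comparison. It deserves correction because the published power, required size and minimum change are wrong, and because the commitment to resize makes the sizing basis a working rule. With controls held at 100, equal-groups sizing over-recruits while its answer is below 100 and under-recruits above that, severely by a historical uptake of 8%.

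**What to change.** Replace the power sentence with one that states the test, sidedness and allocation. For example: with 100 historical controls, 57 evaluable clients give about 95–97% power (two-sided 5%, Fisher's exact or χ² test, unadjusted) for 2% versus 20%, or 80% power for 2% versus about 14–15%. If the corrected formula is retained as the basis, the corresponding figures are 91.5% and about 16%.

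Add that any resizing will use 100 controls and the observed historical rate. If the surplus is meant to cover clinic effects, adjustment or a higher baseline, say so and give the allowance. If the comparison of all eligible catchment-clinic women becomes primary, state the power for that comparison instead.

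The cost is a sentence or two in the sample-size section. No additional participants or data are needed.
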